*Setting and site selection*: We recruited sites (Fig. 2 below) from the Women’s Health Practice-Based Research Network (PBRN), a network that provides a research infrastructure for investigators seeking to increase inclusion of women in VHA research or conduct multi-site women’s focused research in VHA. Comprised of approximately 70 VA sites that see one-half of women Veteran VA users, the PBRN helps investigators overcome the challenges of multi-site studies through the engagement of Site Leads with established working relationships with local clinicians and facility leadership. Sites were also recruited in collaboration with regional leadership in four regional Veterans Integrated Service Networks (VISNs). Each VISN was selected based on leadership’s interest in the EBPs, priorities for women Veterans’ preventive health, and our history of collaboration.

*Low-performing sites*: Our team has a long history of working with sites to improve women Veterans’ health, including QI efforts in low-performing sites. For the current project, a number of our sites are designated low-performing sites based on site visit assessment data.

*Patient eligibility and selection*: Women Veteran VA users are eligible for each EBP as follows: (1) *Virtual DPP*—overweight/obese women Veterans (BMI≥25 kg/m^2^ [≥23 if Asian]) with history of prediabetes (defined as either an HbA1c 5.7-6.5% or fasting blood glucose 100–125 mg/dL or oral glucose tolerance test 140–199 mg/dL) or history of gestational diabetes (GDM) or high risk on diabetes screening questionnaire. Women will receive invitation letters or be referred to the program by a healthcare provider and self-register with a CDC-recognized virtual DPP provider. (2) *TLC*—all women Veterans (who are not pregnant) are eligible to participate in TLC. Women will be referred to the program by a healthcare provider and will receive an outreach call from contracted health coaches to enroll. (3) *ROSE*—All pregnant women Veterans are eligible. Women will be identified and recruited by the site pregnancy/maternity care coordinator or other women’s health staff. As part of each implementation strategy (REP and EBQI, see below), sites will determine their own locally relevant recruitment strategies to engage 40 women Veterans/site in virtual DPP or TLC, and all interested pregnant women in ROSE.

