*Aim 2a: Measures*—These fall into four basic categories shown in Table 2. The *primary outcomes of interest* are access to and engagement in telehealth care for preventive services, measured by referrals and enrollment. We will create composite measures of the proportion of women who participate in preventive telehealth care services for each EBP (# participate/# eligible). The primary outcomes for virtual DPP include the number of women who self-register for DPP (i.e., enroll) and the number who participate in virtual DPP (i.e., complete at least one online DPP module). For TLC and ROSE, the primary outcomes include the number of provider referrals for the programs and number of women Veterans with enrollment encounters. Parallel encounter coding will be developed for ROSE with the guidance of our Office of Primary Care. *Participation and engagement* outcomes collected by EBP are based on the average number of sessions completed and behavior changes documented during the program (e.g., weight change, increase physical activity, depression screens). For virtual DPP, we will assess rates of participation and engagement according to CDC standards for DPP delivery (i.e., average number of sessions attended, proportion who completed ≥9 and ≥16 sessions, etc.). For TLC, rates of participation and engagement are at ≥3 calls and ≥8 calls based on guidance provided by VA national offices regarding meaningful levels of contact with this EBP. For ROSE, maternity care coordinators (or comparable role) and ROSE facilitators will collect data on the number of sessions completed and proportion of completion of postnatal depression screens among participants. The *primary impact performance goals* for the EBPs will be based on performance metrics for telehealth care. For virtual DPP, we will monitor site-level performance measures for participation in weight management programs (e.g., MOVE!). For TLC, we will monitor site-level changes in telehealth encounters for prevention (e.g., Whole Health). For ROSE, we will monitor site-level changes in the use of telemental health and site-level changes in number of prenatal referrals sent out of the VA. Across all EBPs, we will also monitor metrics for use of telehealth services by women Veterans living in rural areas. Secondary outcomes of interest will include *clinical outcomes and other VA performance measures* related to each EBP. For virtual DPP and TLC, we will examine trends in clinical outcomes including percent weight change over 12 and 24 months, prevalence of hypertension, pre-diabetes, and diabetes. We will also examine trends in incident type 2 diabetes (≥1 inpatient diagnosis or any combination of ≥2 within 24 months: A1C≥6.5%, or fasting glucose≥126, or random glucose ≥ 200 or 2-h 75-g oral glucose tolerance test ≥ 200, or outpatient diagnosis code, or anti-hyperglycemic medication claim except metformin) [38, 39]. The VA (HEDIS) performance measures for diabetes and hypertension focus on proportion with guideline-recommended level of control among patients with the condition. Although our project is focused on prevention, we will track these measures because EBPs focused on lifestyle behavior change could impact level of control among diabetics and patients with hypertension. For ROSE, we will examine trends in postpartum attrition from VA among pregnant women through utilization of VA health services in the 12 months post-partum.

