*Data analysis plan for Aim 2a*: We will use generalized linear models to evaluate the effectiveness of the intervention strategies for implementation of the EBPs in increasing women’s participation in telehealth-based preventive care. The models will account for clustering at the site level as well as incorporating site- and patient-level covariates outlined above. The main outcomes will include the composite measures of the proportion of women referred and enrolled in preventive telehealth care services, and the primary independent variable of interest is implementation using REP versus EBQI. We will conduct subgroup analyses by EBP to examine if the effects of the implementation strategies on proportion referred and enrolled vary by EBP (TLC or virtual DPP) as well as evaluate the effect on the *primary impact performance metrics* for telehealth care (weight management programs, Whole Health, and telemental health). In each model, we will examine the potential moderating effects of site-level characteristics (e.g., facility type, size, women’s health care program model, etc.). Adjustment for clustering will be performed using Stata v15, and we will evaluate goodness-of-fit using Mallows statistic (Cp). For DPP and TLC, we will use appropriate generalized linear models to assess weight and behavior change and examine differences by levels of participation (number of sessions completed). For ROSE, we will assess depression scores by levels of participation.

*Power calculations*: We based power calculations on the study’s basic single level of clustering sample design, where sites are randomized to receive either REP or EBQI to implement the EBPs. To detect a moderate effect size in terms of Cohen’s *D* (.26 standard deviations) between REP and EBQI, with 20 sites, and cluster adjustment (ICC=.01) with 80% power we will recruit 40 women per site (total of 800 women). We have considered all 20 sites to be separate clusters in terms of these calculations.

Aims 2b–2d are summarized in Table 3.

**Table 3 Tab3:** Overview of Aims 2b–2d

Method	Timing (per QUERI Roadmap)			Intended analyses
	Pre-implementation	Implementation	Sustainment	
Site tracking log	• Meeting minutes • Templated reflections • Stages of Implementation Completion (SIC)			2b: SIC 2c: Adaptations, experiences of EBP implementation 2d: cost

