It is an innovation and strength of this proposal that we will combine 2b and 2c data sources to link qualitative (via interviews, reflections, etc.) assessments of CFIR constructs with implementation and effectiveness outcomes—including SIC scores for stage, duration, and proportion—for each EBP (virtual DPP, TLC, ROSE) and implementation strategy (REP, EBQI). With the exception of recent work by Palinkas et al., relatively few studies have previously investigated associations between CFIR domains and the stages and timing of implementation milestones achieved [40]. This will enable us to investigate, for example, whether EBQI, a strategy that requires more intensive activity in the initial stages and may thus be slower to reach implementation launch, is associated with improved sustainment, given that sites will be equipped with QI tools beyond the life of the project.

*Aim 2d: Data sources*—In line with current recommendations for budget impact analysis (BIA) for single payers [48] and within VA [49], we will compare costs associated with delivery of usual care with costs for implementation and delivery of our prevention-focused telehealth interventions (virtual DPP, TLC, ROSE) in terms of impact on short-term use of downstream health care resources. For example, we will evaluate whether the cost of implementing the ROSE intervention is associated with cost savings related to a reduction in need for specialty mental health care among women Veterans during the postpartum period.

*Aim 2d: Measures*—Core requirements for BIA include estimates of eligible population, current treatment mix and associated costs, expected treatment mix post-implementation and associated costs, and estimated changes in condition-related downstream costs [50]. Cost estimates for implementation strategies will be informed by site tracking log data (e.g., implementation dose in #hours/per site) as described in *Aim 2c: Data sources*. Healthcare utilization data will be drawn from CDW, as described for *Aim 2a: Data sources*, above.

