*Aim 2d: Analysis*—Analyses will be structured to examine the comparative cost and outcomes of our two implementation strategies, REP and EBQI, as follows [30]: (Cost_Intervention_ + Cost_REP_) − (Cost_Intervention_ + Cost_EBQI_) vs. Outcome_InterventionW/REP_ − Outcome_InterventionW/EBQI_. Qualitative data collected for Aim 2c will also be examined to understand the “qualitative residual” that often remains underexplored in traditional quantitative economic evaluations, aiding in improved cost estimates and understanding of how stakeholders, staff, providers, and implementation teams make sense of implementation need, impact, and cost [30]. For example, cost estimates for an EBP may need to be updated based on adaptations in routine practice reported by providers in interviews. Similarly, leadership across sites may have differing perspectives on whether a higher-intensity strategy, like EBQI, is worth investing in given observed outcomes, with implications for future sustainment and spread efforts.

EMPOWER 2.0 will evaluate the business case for REP and EBQI in implementing DPP, TLC, and ROSE by first drawing upon the Cost of Implementing New Strategies (COINS) method for identifying resources invested in implementation [51]. COINS provides a systematic way of assessing costs associated with each Stage of Implementation Completion (SIC), which provides the blueprint for the business plan [27]. In establishing our cost estimates, we will integrate data from stakeholder interviews, site tracking logs, and reflections to assess costs as they occurred: (a) at each site, (b) for each EBP, (c) for both REP and EBQI, and (d) according to each stage of the implementation effort. As a measure of implementation process, the SIC will be cross-walked with the COINS to develop template plans and timelines for future adopters. Knowing, for instance, that they need to budget for 3 months of pre-launch preparation will allow new sites to plan against their fiscal years, e.g., knowing what to budget when, and what can be spread across different fiscal cycles.

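### The Aim 2d cost formula uses one unindexed intervention cost for both strategies, so any difference in EBP delivery cost between REP and EBQI cancels out

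*Protocol article*

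**What the plan says.** Aim 2d: Analysis introduces the economic comparison with the words "Analyses will be structured to examine the comparative cost and outcomes of our two implementation strategies, REP and EBQI, as follows". The cost side is then "Cost_Intervention_ + Cost_REP_) − (Cost_Intervention_ + Cost_EBQI", and the outcome side set against it is "Outcome_InterventionW/REP_ − Outcome_InterventionW/EBQI". The outcome terms are labelled by strategy; the intervention cost is not.

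Elsewhere in the article:
- Aim 2a: Measures defines the primary outcome through "composite measures of the proportion of women who participate in preventive telehealth care services for each EBP (# participate/# eligible" of women), and the Aim 2a data analysis plan says that "the primary independent variable of interest is implementation using REP versus EBQI".
- Patient eligibility and selection asks sites to "engage 40 women Veterans/site in virtual DPP or TLC, and all interested pregnant women in ROSE". DPP and TLC therefore have a common target, and ROSE has no number.
- Table 2 lists the average number of sessions completed as an engagement measure for each EBP.
- Aim 2d: Data sources brings delivery cost into scope, but in a budget impact comparison with usual care.
- Aim 2d: Analysis adds that "cost estimates for an EBP may need to be updated based on adaptations in routine practice reported by providers in interviews".

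**The concern.** A cost comparison of two implementation strategies should charge each strategy for what it causes to be spent. That includes delivering the EBP to the women it brings in. As printed, the formula lets outcomes vary by strategy but holds delivery cost common to both. If one strategy enrols more women or keeps them for more sessions, the gain shows on the outcome side and the spending that produced it does not show on the cost side.

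The comparison has a declared use. The section on EBQI asks when investment in a high-intensity strategy is warranted, and the Discussion offers the cost findings as support for resource allocation. A health system that adopts the strategy with more uptake also has to pay for the extra delivery.

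**Working it through.** **Inputs from the article.** The formula (Aim 2d: Analysis); 10 sites per strategy (Randomization); 40 women per site in DPP or TLC (Patient eligibility and selection; Power calculations). The target is thus 10 × 40 = 400 women per arm. The article states no cost figure, so there is none to reproduce.

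**Inputs assumed for illustration.** Delivery cost per woman c from 0 to 1,000 dollars; Cost_REP = 100,000 and Cost_EBQI = 200,000 dollars; numbers engaged as shown below.

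**Step 1: the printed formula.** Write C for the intervention cost.

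`(C + Cost_REP) − (C + Cost_EBQI) = Cost_REP − Cost_EBQI`, whatever the value of C.

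**Step 2: the same contrast with delivery cost taken in its own arm.** With a common unit cost c and n women per arm:

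`(c·n_REP + Cost_REP) − (c·n_EBQI + Cost_EBQI) = (Cost_REP − Cost_EBQI) + c·(n_REP − n_EBQI)`

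The last term is what the printed formula leaves out. If unit cost also differs by arm, through sessions or adaptation, the omitted term is c_REP·n_REP − c_EBQI·n_EBQI.

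**Step 3: numbers.** The printed contrast is 100,000 − 200,000 = −100,000 in every row.

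| c (assumed) | n_REP | n_EBQI | Omitted term | Arm-specific contrast |
|---|---|---|---|---|
| any | 400 | 400 | 0 | −100,000 |
| 0 | 400 | 500 | 0 | −100,000 |
| 100 | 400 | 500 | −10,000 | −110,000 |
| 500 | 400 | 500 | −50,000 | −150,000 |
| 1,000 | 400 | 500 | −100,000 | −200,000 |
| 100 | 400 | 600 | −20,000 | −120,000 |
| 500 | 400 | 600 | −100,000 | −200,000 |
| 1,000 | 400 | 600 | −200,000 | −300,000 |

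The first row is the article's own equal target. There the DPP/TLC volume term vanishes.

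**Step 4: per extra woman engaged.** The article sets a cost difference against an outcome difference and does not define a ratio. A reader who forms one for 400 versus 500 women gets −100,000 / −100 = 1,000 dollars from the printed formula. The arm-specific form gives 1,100, 1,500 and 2,000 dollars at c = 100, 500 and 1,000. The shortfall is exactly c.

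**The case against.** The strongest reply is that the formula is schematic. It follows a cited method in a condensed article, and a constant written into both brackets would serve no purpose, so the authors may have meant each arm's own delivery cost. The remark that EBP cost estimates may be revised for adaptations suggests that intervention cost is not treated as a fixed constant. Aim 2d: Analysis also says that costs will be assessed as they arise by site, EBP, strategy and stage. Aim 2c: Measures says that the site logs will support cost estimates at the first three of those levels.

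Part of this stands. The fault lies in the stated contrast and not necessarily in the data to be collected. But the sentence on costs as they arise follows the description of COINS, which covers resources put into implementation. The adaptation remark does not mention strategy. Nowhere does the article give the intervention cost a value specific to REP or EBQI. If that is what is meant, the formula should say so.

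Three stronger readings are tempting and are not supported:
- **That the plan says uptake or delivery will differ by strategy.** It does not. It tests for a difference, and the DPP/TLC target is the same in both arms.
- **That the whole economic comparison is biased towards the strategy with more uptake.** The net direction is undetermined. Aim 2d: Data sources raises possible savings from less specialty mental health care under ROSE, and such savings could offset the extra delivery cost.
- **That downstream costs are wrongly left out of the formula.** Aim 2d: Measures lists "estimated changes in condition-related downstream costs" among the requirements of the budget impact analysis, so they are handled there.

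**Conclusion.** The point holds for the formula as printed: the intervention cost cancels identically, and the cost side is the difference in strategy cost alone. Any difference between arms in EBP delivery cost is omitted. At a common unit cost, the omission understates the relative cost of the strategy that engages more women, on the delivery-cost component only.

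Its size cannot be fixed from the article. It is 10,000 to 200,000 dollars for an assumed c of 100 to 1,000 and a difference of 100 to 200 women, and zero if volume, sessions and unit cost are equal in both arms. Reaching the common target of 40 women per site would remove the DPP/TLC volume part, but sessions completed and ROSE numbers could still differ.

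This concerns an economic sub-aim. The primary outcome, its analysis and the sample size are untouched.

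**What to change.** Index the intervention cost by strategy, as the outcomes already are:

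`(Cost_InterventionW/REP + Cost_REP) − (Cost_InterventionW/EBQI + Cost_EBQI)`

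State that each intervention cost is measured in its own arm, over the same population and time window as the outcome difference.

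If the authors intend a comparison of strategy cost only, drop the intervention term, say so, and note that the result does not include the cost of delivering the EBP to additional women.

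The cost of the change is a corrected line of text, plus unit delivery costs attached to data already planned: session counts from each EBP, site tracking logs and CDW utilization. No new sites, participants or visits are needed.

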### Aim 3: Generate implementation “playbooks” for program partners that are scalable and serve as guidance for future implementation of a broader array of evidence-based women’s health programs and policies

Implementation evaluation of process and outcomes across EBPs, actively supported by the Implementation Core (see below), will contribute to the development of implementation playbooks—brief, user-friendly summations of implementation targets, processes, outcomes, and recommendations for sustainment, scale up, and spread [52]. EMPOWER 1.0 was an early QUERI champion for playbooks and has provided a laboratory for examining what kinds of information playbooks should contain for optimum utility and impact. For EMPOWER 2.0, we will work collaboratively with sites and partners to develop operations playbooks, brief “tip sheets”, and other operations-focused implementation support products as needed.

## Discussion

EMPOWER 2.0 provides a model for the conduct of a hybrid type 3 effectiveness-implementation trial comparing two implementation strategies in a large healthcare system. It is a limitation of this study that it is being conducted entirely within the VA healthcare system and thus results may not generalize; however, site- and regional-level conditions within the VA vary considerably, and we anticipate that findings will speak to common challenges in addressing the unique needs and resources of local settings.

Although this proposal was developed and submitted for funding prior to the COVID-19 pandemic, recent events have only highlighted the need for increased telehealth services and significantly expanded remote care technology integration within and outside of the VA. Pre-existing gaps faced by many healthcare systems in the uptake and reach of preventive care services have been amplified during the pandemic, exacerbated by the deferral of care for non-COVID-19 conditions [53–55]. The emphasis of this study on the implementation of preventive care services is thus an important strength, particularly as this has traditionally been an underdeveloped area of implementation science [56, 57].

As relatively few studies have compared the effectiveness of implementation strategies for achieving rollout of evidence-based interventions across large healthcare systems, the proposed rigorous comparison of clinical benefit, cost and return on investment, and time to achieving implementation associated with REP and EBQI will be of value in directly supporting evidence-based policy and resource allocation decisions. Our program will not only enhance care for women Veterans across 20 VA sites, but will also shed fundamental insights on implementation strategies to help sustain these improvements and inform broader dissemination across and beyond VA.

## Data Availability

Not applicable.

## Abbreviations

BIA: Budget impact analysis
CDW: Corporate Data Warehouse
CFIR: Consolidated Framework for Implementation Research
COINS: Cost of Implementing New Strategies
DPP: Diabetes Prevention Program
EBP: Evidence-based practice
EBQI: Evidence-Based Quality Improvement
EMPOWER 2.0: Enhancing Mental and Physical Health of Women Veterans through Engagement and Retention 2.0
QUERI: Quality Enhancement and Research Initiative
PACT: Patient-aligned clinical team
REP: Replicating Effective Program
ROSE: Reach Out, Stay Strong Essentials
SIC: Stages of Implementation Completion
TLC: Telephone Lifestyle Coaching
